## Abstract

**Background:**

Rehabilitation for children with hemiplegic cerebral palsy (HCP) aimed to improve function of the impaired upper limb (UL) uses a wide range of intervention programs. A new rehabilitative approach, called Action-Observation Therapy, based on the recent discovery of mirror neurons, has been used in adult stroke but not in children. The purpose of the present study is to design a randomised controlled trial (RCT) for evaluating the efficacy of Action-Observation Therapy in improving UL activity in children with HCP.

**Methods/Design:**

The trial is designed according to CONSORT Statement. It is a randomised, evaluator-blinded, match-pair group trial. Children with HCP will be randomised within pairs to either experimental or control group. The experimental group will perform an Action-Observation Therapy, called UP-CAT (Upper Limb-Children Action-Observation Training) in which they will watch video sequences showing goal-directed actions, chosen according to children UL functional level, combined with motor training with their hemiplegic UL. The control group will perform the same tailored actions after watching computer games. A careful revision of psychometric properties of UL outcome measures for children with hemiplegia was performed. Assisting Hand Assessment was chosen as primary measure and, based on its calculation power, a sample size of 12 matched pairs was established. Moreover, Melbourne and ABILHAND-Kids were included as secondary measures. The time line of assessments will be T0 (in the week preceding the onset of the treatment), T1 and T2 (in the week after the end of the treatment and 8 weeks later, respectively). A further assessment will be performed at T3 (24 weeks after T1), to evaluate the retention of effects. In a subgroup of children enrolled in both groups functional Magnetic Resonance Imaging, exploring the mirror system and sensory-motor function, will be performed at T0, T1 and T2.

**Discussion:**

The paper aims to describe the methodology of a RCT for evaluating the efficacy of Action-Observation Therapy in improving UL activity in children with hemiplegia. This study will be the first to test this new type of treatment in childhood. The paper presents the theoretical background, study hypotheses, outcome measures and trial methodology.

**Trial Registration:**

NCT01016496

## Background

Cerebral palsy (CP) is "a group of disorders of the development of movement and posture causing activity limitation that are attributed to non-progressive disturbance that occurred in the developing foetal or infant brain. The motor disorders of CP are often accompanied by disturbance of sensation, cognition, communication, perception, and/or behaviour, and seizure disorder" [1]. Therefore, children with CP are faced with a variety of motor and sensory impairments that have an impact on their arm function [1,2]. It is the most common cause of physical disability in childhood, occurring between 2 and 3 per 1000 live births. Hemiplegic forms, characterised by a clinical pattern of unilateral motor and sensory impairment, constitute the most frequent expression of CP (more than 38% of cases) and the second in term of prevalence, after diplegia, in premature infants (around 20% of cases) [3-5]. Typically, the upper limb (UL) is more involved than the lower one, resulting in a significant reduction of the effective use of the arm and hand in the daily activities in terms of activity and participation limitations.

There are many models of intervention targeting deficits in UL function that aim to reduce activity limitations for children with hemiplegia. In a recent review [6] the authors identified four main interventions: intramuscular botulinum toxin A (BoNT-A) combined with upper-limb training; constraint-induced movement therapy (CIMT); hand-arm bimanual intensive training (HABIT) and neurodevelopmental therapy. They demonstrated that no one treatment approach seems to be superior; however, injections of BoNT-A provide a supplementary benefit to a variety of upper limb-training approaches. Both CIMT and HABIT rely on UL intensive training, either unimanual or bimanual, respectively. They are underpinned by theories of motor learning and neuroplasticity that describe a correlation between improved motor function and the use of "massive" or "repetitive" practice.

A possible new rehabilitative approach aimed to improve movement control of the UL is based on the discovery of mirror neurons (MNs) in the ventral premotor cortex (area F5) and in the inferior parietal lobule (area PFG) of the monkey. They constitute a class of visuomotor neurons discharging both when a monkey performs a goal-directed motor act (e.g. grasping an object) and when it observes another individual performing the same or a similar motor act [7-9].

A comparable Mirror system (MS) has been identified also in humans, using several techniques such as Positron Emission Tomography (PET), functional Magnetic Resonance Imaging (fMRI) and Trancranial Magnetic Stimulation (TMS). The two main nodes of human MS are the inferior parietal lobule (IPL) and the ventral premotor cortex (PMv), plus the caudal part of the inferior frontal gyrus (IFG) (see for review Rizzolatti et al 2009 [10]). This network transforms the sensory representations of observed motor acts into their motor representations. This discovery has radically changed the notion of well-separate neural substrates for sensory and motor processing by suggesting that perception and action are much more tightly linked than previously believed [11]. Note that the *mere observation *of motor acts performed by other individuals determines a clear increase in activity in the above-mentioned fronto-parietal neural network. Moreover, when TMS stimulation is delivered during action observation, it produces an increase in the excitability of the corticospinal pathway (i.e. increased amplitude of motor evoked potentials [MEPs]) and the recorded pattern of muscle activation is very similar to the pattern of muscle contraction recorded during the execution of the same action [12]. On the basis of the mechanism matching action observation with action execution, it has been postulated that the MS is the basis for action understanding and imitation. These functions make it a very good candidate for observational learning [11,13-15].

An important characteristic of MNs is that most of them discharge in association with specific motor acts (e.g., grasping, holding, tearing) rather than with the simple movements [8,9]. This goal-directed activity relies on the fact that MNs are basically motor neurons and it is well known that the premotor areas and, in part, even primary motor cortex (M1) encode the goal of a given motor act [16-19].

This concept has been recently further supported by two studies on premotor grasping neurons recorded in monkeys trained to use two types of pliers (normal and reversed) that allowed to obtain the same goal (grasping food) by performing opposite movements. In a first study it has been found that these neurons fire when the monkey uses both types of tools to grasp the food, showing that the activity is related to the goal of the motor act and not to the movements (fingers flexion or extension) the monkey used to achieve it [20]. Moreover, in a second study [21] it was demonstrated that after the training for the use of pliers, all neurons responding to the observation of hand grasping also responded to the observation of grasping with pliers and many of them also to the observation of another, different tool, to which the monkeys were not trained (spearing with a stick). These results showed that both tools were effective in triggering MNs, in spite of the fact that they markedly differed from one another (as well as from the hand, the natural grasping effector) both in their visual aspects and in their movement kinematics. In other words, it is plausible that, once a general set has been learned, a generalisation occurs to other implements, even to those the monkey has never used. This finding could have an important rehabilitative relevance, because by amplifying the tools the patients will enrich their use of UL.

Motor acts are normally combined to form goal-related actions. Interestingly, the same motor acts can be included in different actions having different ultimate goals. Recently, it has been shown that the visual responses of a subset of premotor and inferior parietal MNs, studied during both the observation and execution of grasping acts embedded in different actions (e.g., grasping to place or grasping to eat), are modulated by the final action goal (placing or eating) [22,23]. Altogether, these data indicate that during observation of an agent performing an action, the observer codes the final goal of the observed action (corresponding to the agent's intention) and the goal of the motor act included in that specific action. These two aspects are fundamental for a rehabilitation therapy based on action observation.

An important assumption for an observation-based therapy is the plasticity of the MS. Several studies [24-26] indicate a strong role of the MS in representing previously acquired motor skills. These fMRI studies examined the mirror activations in person expert in specific motor skills (dance) and compared them with the activations determined by the same stimuli in individuals having different motor experience. The results showed that the observed dance steps were mapped onto the observers' premotor-parietal motor system and that the activation was stronger in individuals expert in performing them. Thus, during observation, observers tend to 'resonate' more strongly with actions already embodied in their own motor repertoire.

These data prompt the hypothesis that if observation is accompanied by imitation one should expect a higher activation of the MS. In a fMRI study where non-guitarists were asked to imitate unfamiliar guitar chords (a task chosen to represent the initial stage of imitation learning) Buccino et al [27] demonstrated that the basic circuit underlying this capacity includes the MS that starts to be active during the observation of the guitar chords and it is permanently active also during motor preparation and execution. Moreover, the left dorsolateral prefrontal cortex (DLPFC, most likely area 46) was found activated mainly during motor preparation of imitative execution, suggesting its possible role in the selection and recombination of the individual motor elements, as represented in the MS, into a new motor pattern.

These findings were confirmed by a more recent study conducted by Vogt et al [28] showing that MS is more strongly involved during the observation of novel actions than of previously practised actions.

The possibility to use for neurological patients an observation/imitation approach in the Action-Observation Therapy has been exploited in two studies with hemiplegic adults after stroke. In the first clinical trial, Ertelt et al [29] enrolled 16 participants with moderate post-stroke hemiparesis who were randomly assigned to either the experimental or the control group. The experimental group performed an action-observation training based on the combination of action observation with repetitive motor training of the observed actions for 90 minutes per day with the paretic hand. Actions of increasing complexity were observed and imitated each day for 18 days. The control group performed the same UL actions of the experimental group on verbal instruction, while they observed only geometrical symbols and letters. Significant functional improvement on standard scales occurred for experimental group compared with controls and was maintained at 8 weeks post-training. In addition, before and after training, participants of both groups performed an independent object manipulation task while scanned with fMRI. The data revealed, only in the experimental group, a significant increase in neural activity of motor-related brain regions including the MS. More recently, Franceschini et al [30] performed an observational study, without control group, with twenty-eight chronic stroke patients with UL impairment. All patients underwent for four weeks, five days a weeks, a rehabilitation treatment based on observation of video-clips presenting hand daily actions, followed by the imitation of those same actions with the affected limb. In all function scales, scores improved significantly after treatment and changes were maintained also after two-months.

To date, there are no studies using action-observation model in children. In this project, we will propose, for the first time, a new paradigm of UL rehabilitation, called Upper Limb Action-Observation Training (UP-CAT), built as a randomised controlled trial (RCT) according to Consolidated Standards of Reporting Trials (CONSORT) Statement for Randomised Trials of non-pharmacologic treatment guidelines [31,32] to examine the efficacy of Observation To Imitate (OTI) in improving the UL activity in children with Hemiplegic Cerebral Palsy (HCP).

## Methods/Design

The following hypotheses will be tested by means of a RCT comparing the effects of UL action observation versus physical practice in improving the UL activity in children with HCP:

• If the MS works in terms of action goals, regardless of the kinematic properties, there will be a better improvement in the goal of UL use rather than in the kinematics of UL;

• OTI will be able to induce more changes in UL activity than those due only to the physical practice of the same actions;

• OTI will result in greater enhancement of daily activity performance;

• OTI will result in a greater mirror circuit re-organisation compared to action execution only and this cortical plasticity will be retained for longer periods.

These experimental hypotheses will address the following specific aims:

• OTI model is a novel training method where the main core is to observe an UL performing tailored goal actions, with the intent to imitate. This study will determine if this model is useful to enhance activity performance and, if there are improvements, for how long that effect will be retained;

• If OTI model will enhance the activity performance, new models of the rehabilitation setting in clinical practice will be proposed;

• If OTI model results in greater brain plasticity, the functioning of MS and its role in learning also in children with brain lesion will be demonstrated;

• If OTI model will be a good tool, it will guide practice also in other disabilities.

### Study design

A matched pairs randomised, evaluator-blinded trial will be carried out using an action-observation intensive training program to evaluate the efficacy of OTI compared to physical practice only in children with HCP aged 5 to 15 years. Assessment will be performed at baseline (T0, on the week preceding the onset of the treatment), and then on the week (T1) and 8 weeks (T2) after the end of the treatment. A further assessment will be performed at 24 weeks (T3) after the end of the treatment to evaluate the retention of effects.

The experimental design and outcome measures are depicted in Figure 1.

**Figure 1 F1:**
[figure not shown]
**Flow-chart of UP-CAT study according to CONSORT guidelines**. Abbreviations: AHA: Assisting Hand Assessment MUUL: Melbourne Assessment of Unilateral Upper Limb Function fMRI: functional Magnetic Resonance Imaging * only in a subgroup of children enrolled.

### Study sample and recruitment

Potential participants will be identified according to strict criteria, listed below, from hemiplegic children' databases of the Department of Developmental Neuroscience of the IRCCS Stella Maris (Pisa, Italy) and of Unit of Children Rehabilitation of S. Maria Nuova Hospital (Reggio Emilia, Italy). Suitable children and their parents will then be invited to participate in the randomised trial and informed consent to participate will be obtained from the child and/or by her/his parents prior to enrolment in the RCT.

The trial has been approved by the Ethics Committee of both Institutions.

#### Inclusion criteria

This study will include children if they met the following criteria:

• confirmed diagnosis of HCP according to 2005 definition (MRI and clinical history) [33];

• aged 5 to 15 years at time of recruitment;

• predominant spasticity rather than dystonia interfering with UL function according to the classification of motor type by Sanger et al [34] with Modified Ashworth scale (MAS) grade ≤ 2 [35];

• mild or moderate severity of UL disability i.e. active use of affected UL from poor active assist use to complete spontaneous use according to House Functional Classification System [36,37] grade between 4 and 8;

• sufficient cooperation and cognitive understanding to participate in the activities;

• good attention;

• no sensory impairment;

• no history of seizures or seizures well controlled by therapy;

• children living near to one of the two clinical centres (Pisa or Reggio Emilia);

• parents able to commit to an intensive therapy program for 3 weeks.

For a subgroup of children performing fMRI further inclusion criteria will be i) sufficient cooperation to perform imaging studies for 45 minutes and ii) no exclusions for 1.5 Tesla Magnetic Resonance System such as no metal implants, no shunts.

#### Exclusion criteria

• moderate or severe muscle spasticity and/or contracture (MAS > 2) [35] which would require spasticity management or orthoses;

• activity level at House Functional Classification System [36,37] < 4;

• uncontrolled epilepsy;

• previous orthopaedic surgery in the UL;

• BoNT-A injection in the UL within 6 months prior to study entry.

### Sample size

According to CONSORT guidelines [31,32] the sample size estimates were based on projected treatment effect on the primary outcome measure, the Assisting Hand Assessment (AHA). The AHA scale's responsiveness to change has been shown in a study in which Eliasson et al [38] used the scale as the outcome measure in evaluating the effects of a modified model of CIMT. The authors reported a significant effect size of 1.16. Calculation by a statistician indicated that in order to detect a 1.16 effect size at significant level of 0.05 and 80% power a minimum sample size of 12 per group is required in our study.

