**Figure 2 F2:**
[figure not shown]
**Layout of Study Treatment**.

Children randomised in the control group will match the design of experimental session except for the content of the videos showing computer games with no biological movements (Figure 2). Moreover, the children will play the games without using their hands, i.e. the person of the staff will use the keyboard to go on over the game. Following verbal instruction given by the staff, control group will carry out the same exercises in the exact order performed by the experimental group.

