### Analyses

Clinical Data will be managed and analysed using the Statistical Package for Social Sciences (SPSS version 16.0). Descriptive statistics (means, standard deviation) will be calculated to summarise the data set for both groups and to identify potential baseline differences between the groups; p values will be used to indicate the strength of the evidence, a significant level of 0.05 will be used. Initially between group differences will be evaluated at baseline (T0) assessment point using Mann-Whitney U independent sample test for all Outcome Measure chosen. Within group changes between baseline and follow-up assessment (T1 and T2) will be evaluated using Wilcoxon matched-pairs sign rank test. A second level analysis with independent sample t test of the differences between the follow-up assessment and baseline (T1 vs T0 and T2 vs T0) will be performed for the comparison of the rehabilitative gain between the two groups. Moreover, Cohen's d values and their 95% confidence interval will be calculated to obtain a pre-post intervention effect size [70]. According to Cohen's work values of effect size below 0.2 will be considered to reflect "no effect", values from 0.2 to 0.5 a "small effect", values between 0.5 and 0.8 a "medium-sized effect", and values > 0.8 "large effect".

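### The 80% power figure uses an effect from a constraint-therapy study, not the gain over matched practice tested here; at 1.16 the planned t test gives 77.5%

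*Protocol article*

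**What the plan says.** Under Sample size, the article bases the calculation on the AHA, the primary outcome. It refers to a study that "used the scale as the outcome measure in evaluating the effects of a modified model of CIMT" and adds: "The authors reported a significant effect size of 1.16." From this it derives its requirement: "in order to detect a 1.16 effect size at significant level of 0.05 and 80% power a minimum sample size of 12 per group". The Abstract turns the result into the design: "a sample size of 12 matched pairs was established".

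The contrast is set out elsewhere. The hypotheses under Methods/Design ask whether observation with intent to imitate changes upper limb activity more than practising the same actions alone. Study treatment (text at Figure 2) says that the "control group will carry out the same exercises in the exact order performed by the experimental group"; the sessions differ in what the child watches beforehand.

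Under Analyses, the between-group comparison of gains is "A second level analysis with independent sample t test of the differences between the follow-up assessment and baseline", at T1 and at T2, and "a significant level of 0.05 will be used". Sidedness is not stated.

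**The concern.** A power statement is informative only if the planning effect refers to the comparison that will be tested. Here the effect belongs to a different therapy and is brought in as evidence that the AHA can register change. The article does not say what that therapy was compared with, or whether 1.16 is a between-group or a pre-post effect. On either reading it is not an estimate of what watching goal-directed actions adds to identical practice. An active, matched control arm may itself improve, and only the excess counts towards the trial's question.

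The second issue is numerical. With 12 per group the t test has 22 degrees of freedom, and at that size the normal formula flatters the power by a few points.

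At stake is how the result is read. Someone who accepts 80% power at face value would give a non-significant result more weight against action observation than the design can bear, unless the true increment is about 1.2 standard deviations or more.

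**Working it through.** **Inputs**

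| Input | Value | Source |
|---|---|---|
| Standardised effect, d | 1.16 | Sample size |
| Significance level | 0.05 | Sample size; Analyses |
| Sides | two (assumed; not stated) | – |
| Target power | 80% | Sample size |
| Children per group, n | 12, allocated 1:1 within pairs | Sample size; Abstract |
| Between-group test | independent-sample t test on change from baseline | Analyses |
| Smaller increments | 1.0, 0.8, 0.5 (assumed) | not in the document |

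**Step 1. Reproduce the stated size.** Normal approximation for two means:

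n = 2(1.960 + 0.842)² / 1.16² = 11.67, rounded up to 12 per group.

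The matching power at n = 12 is Φ(1.16 × √(12/2) − 1.960) = Φ(2.841 − 1.960) = Φ(0.881) = 81.1%. The stated 12 therefore reproduces. The article does not name its method; that it used this formula is inferred from the matching number.

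**Step 2. Use the planned test.** For an independent-sample t test, degrees of freedom = 2 × 12 − 2 = 22 and the noncentrality parameter is 1.16 × √(12/2) = 2.841. The two-sided noncentral-t calculation gives:

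- power at n = 12: 77.5%, which is 2.5 points below 80%
- n needed for 80%: 12.70, so 13 per group (power 81.0%)
- effect detectable with 80% power at n = 12: d = 1.20

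**Step 3. Vary the unstated or alternative choices at d = 1.16, n = 12.**

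- One-sided t test: 86.6%.
- Paired analysis, if it were used: about 73% with within-pair correlation 0 and 82% with correlation 0.2 (both assumed). The article names an independent-sample test, so this is context only.

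**Step 4. Power for other increments, n = 12, two-sided t test.**

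| Increment d (assumed) | Power | n per group for 80% |
|---|---|---|
| 1.0 | 64.9% | 17 |
| 0.8 | 46.6% | 26 |
| 0.5 | 21.6% | 64 |

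The last two values are cut-points on the article's own effect-size scale under Analyses, where 0.5 to 0.8 is medium-sized and above 0.8 is large. They are not predictions of what action observation will achieve.

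**Step 5. Compare planning effect and test.** The 1.16 describes a constraint-therapy programme on the AHA. The hypotheses, the control condition and the between-group t test all concern the difference between two arms doing the same exercises. Nothing in the article links the two quantities.

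**The case against.** **The 2.5-point gap is minor.** It amounts to one child per group, the usual formula does give 12, and a one-sided test would exceed 80%. This stands: it is a small-sample shortfall and not a gross error, and 77.5% depends on assuming two sides. It does not touch the source of the 1.16.

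**An increment near 1 is not implausible on the article's own background.** The Background describes a randomised trial in 16 adults after stroke, comparing action observation with a control group doing the same actions and reporting significantly greater improvement. If it was split 8 and 8 and analysed by a two-sided t test (both assumed), significance required an observed d of at least 2.145 × √(2/8) = 1.07. This also stands as context, and it is a reason not to present the small increments as the likely ones. But that trial was small and in adults, and the article does not use it to justify 1.16.

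**Estimation is already planned.** Analyses treats p values as strength of evidence and plans Cohen's d with 95% confidence intervals. This is partly right, and the article nowhere says that a non-significant result will be taken as no benefit. However, the planned d is described as a pre-post effect size, which is not the between-group difference.

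**Two stronger readings do not hold.** A reader might infer that large benefits would usually be missed. Power passes 50% at d of about 0.84 and is 65% at 1.0 and 73% at 1.1, so this is true only at the very bottom of the article's large band. A reader might also fault the absence of an allowance for loss to follow-up. A condensed article may leave that to the full protocol, and no loss rate is given, so it is not raised here.

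**Conclusion.** The concern holds in two parts of unequal weight.

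The main part is that the planning effect of 1.16 is not tied to the trial's contrast. This rests on the text alone and does not depend on whether 1.16 was a between-group or a pre-post effect. Its size depends on the true increment, which the document does not give; the range in the working runs from 77.5% power at 1.16 down to about 22% at an assumed 0.5.

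The lesser part is that, even at 1.16, the planned test falls slightly short of the stated 80%, assuming a two-sided test.

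Neither part shows that 24 children is an unacceptable size for a first trial of this therapy in children. What is not supported is the unqualified 80%.

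**What to change.** Keep 24 children and replace the power statement under Sample size with wording such as:

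> Twelve children per group give about 78% power at d = 1.16 and 80% at d = 1.20 for the between-group difference in AHA change (two-sided independent-sample t test at 0.05), and about 65% at d = 1.0, 47% at d = 0.8 and 22% at d = 0.5 (assumed increments). The value 1.16 comes from a CIMT study and is not an estimate of the increment over matched practice.

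Under Analyses, add that the between-group difference in AHA change will be reported with its 95% confidence interval, and that a non-significant result will be interpreted from that interval and not as absence of effect.

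The cost is a change of wording and a less favourable stated power. No extra children, assessments or changes to the planned test are needed.
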